
#### Secondary Objective 5: Estimating the Costs and Resource Use

For each intervention, descriptive statistics will be used to characterize the categories of the estimated costs (ie, mean [SD] or median [IQR] as appropriate). In this study, missing data costs will be replaced by means or medians, as appropriate. We will quantify uncertainties by reporting the differences between the means and 95% CIs for the categories of the comparator groups’ estimated costs and then interpret the levels of uncertainty based on these [28] and by conducting statistical tests (ie, a *t* test or Mann-Whitney *U,* test as appropriate), while looking for differences in each category of estimated costs between the comparator groups. All α levels of significance will be set at *P*≤.05 (two-tailed).

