### Outcome Variables

#### Primary Objective and Secondary Objectives 1 to 4: Primary Outcome Variables

The retention rates and intervention compliance will be calculated for the primary objective. The retention rates will be calculated according to the participants’ discontinuation of the interventions and their absence at the posttest at week 10. Intervention compliance means all of the hand rehabilitation sessions are completed by each group [21]. This study’s primary outcome variables for secondary objectives 1 to 4 are related to range of motion and strength: (1) AROM and PROM of wrist flexion and extension and forearm pronation and supination, (2) grip strength, and (3) pinch strength.

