**Measurements of economic evaluation**													
	Costs	N/A^h^		Questionnaire for costs associated with use of the FEPSim and provision of the intervention		✓						✓	

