### Sample Size

#### Primary Objective and Secondary Objectives 1 to 4

As this is a feasibility study, a sample size calculation is not required [17]. However, we can estimate the number of participants we will be able to recruit during the data collection period. According to the clinical partners at the 2 hospitals involved in this study, approximately 167 patients who potentially meet the inclusion criteria will be admitted (accessible population). We aim to recruit 47 participants for each group, for a total sample size of 94 participants, to compensate for a 30% dropout rate. Thus, the recruitment of 94 participants represents 56.3 % (94/167) of the participation rate. This number is based on our ability to detect a small effect size (Cohen *d*=0.25) with 80% power and an α of .05 (two-sided). The sample size calculations were estimated using G*Power software version 3.1.9.4 (Universitat Kiel) [23].

#### Secondary Objective 6

Ten hand therapists from the hand therapy services who have used the FEPSim device will be recruited. Individual interviews will be conducted until either redundancy or theoretical saturation of the data has been achieved [24].

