#### Secondary Objective 5: Estimating the Costs and Resource Use

To estimate the resource use and costs, we will use a single study–based economic evaluation approach (patient-level data). The costs will include resources related to the following categories: (1) the time human resources spend on the sessions will be monitored during the study, whereas the information on the average salaries of the human resources will be taken from the records at each hospital; (2) the capital cost of the equipment used in each intervention and depreciation of the equipment will be calculated using the straight-line depreciation approach; (3) therapeutic supplies (eg, weights and elastic or squeezing supplies); (4) consumables (eg, bandages and sanitization wipes); (5) cost of sterilization, if needed; (6) allowance costs (if any); and (7) maintenance costs (eg, calibration, preventive, and corrective maintenance of equipment). The information on the costs will be taken from the financial records at each hospital. In addition, we will conduct face-to-face interviews with the financial departments at both hospitals to identify the cost components and costing method.

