### Withdrawal From the Study

The participants and substitute decision makers can request to withdraw from the study at any time, either verbally or in writing. The participants will be able to withdraw from the study at any time before the group analysis is calculated. If a participant withdraws, their information will not be taken into account for analysis. In the event that a participant requests to have their data destroyed, the research team will honor this request by shredding and recycling the paper records and erasing any records stored on a computer hard drive using commercial software apps designed to remove all data from storage devices. However, once all the participants’ data have been analyzed, a participant cannot withdraw. The participants will be informed of this in the consent letter. The deadline for withdrawal will be once all the participants’ data have been collected and the data analysis is underway. This will be around the 16th month of the study.

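### Single mean or median replacement of missing costs, uncapped and with no named reference group, makes the cost confidence intervals too narrow and can distort the difference between arms

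*Protocol article*

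**What the plan says.** Under Data Analyses, Secondary Objective 5, the protocol article states: "In this study, missing data costs will be replaced by means or medians, as appropriate". The same paragraph then reports mean differences with 95% CIs for each cost category, and applies a t test or Mann-Whitney U test, "looking for differences in each category of estimated costs between the comparator groups", at a two-tailed 5% level.

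Other sections that bear on this rule:

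- **Data Collection Methods, Secondary Objective 5.** Costing uses patient-level data, and "the time human resources spend on the sessions will be monitored during the study". Salaries and other prices come from hospital records.
- **Data Collection Methods, Secondary Outcome Variables.** Therapists record how long and how frequent the sessions are in both groups.
- **Table 1.** The cost instrument is "Questionnaire for costs associated with use of the FEPSim and provision of the intervention", scheduled at T0 and T3 only. Its participants entry is N/A.
- **Outcome Variables.** Retention counts "discontinuation of the interventions and their absence at the posttest at week 10".
- **Sample Size.** "We aim to recruit 47 participants for each group, for a total sample size of 94 participants", a number chosen "to compensate for a 30% dropout rate".
- **Withdrawal From the Study.** "If a participant withdraws, their information will not be taken into account for analysis".
- **Data Analyses, Primary Objective and Secondary Objectives 1 to 4.** Analyses follow intention to treat. Simple imputation of clinical outcomes is limited to less than 10% missing and uses the average within the medical-condition stratum.

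**The concern.** Replacing a missing value with one fixed number adds no information, yet the later formulas count it as an independent observation and see less spread than there is. The stated 95% CIs and P values then overstate what is known. This matters because the article intends to interpret uncertainty in the cost comparison from those intervals, and to offer the results to people who make purchasing decisions.

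Two features make it worse. There is no limit on how much may be filled, whereas the clinical rule in the same section has one. There is also no named reference group, whereas the clinical rule names the stratum. The wording allows an arm mean, a stratum mean, a pooled mean or a median, and these do not give the same answer.

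A further question is what counts as a missing cost. Early stopping is foreseen, and the cost paragraph does not say that the cost accrued before stopping is kept or that sessions not held cost nothing. If a stopper's total were treated as missing, the fill would replace a real, lower cost with one typical of finishers.

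**Working it through.** The article gives no unit cost, cost SD or expected cost difference, so there is no stated figure to reproduce. The checks below show how the rule behaves.

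**1. Interval width under an arm-mean fill**

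Inputs: n = 47 per arm (Sample Size). The number filled is assumed. The largest case, 14 of 47, comes from applying the 30% dropout allowance (0.30 × 47 = 14.1). That allowance is not a missing-cost rate, so smaller cases are shown as well. Values are assumed missing at random within arm, so the correct standard error is that of the m observed values.

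Filled values add nothing to the sum of squares, so the SD shrinks by sqrt((m−1)/(n−1)). Dividing by sqrt(n) and not sqrt(m) shrinks the standard error by a further sqrt(m/n). With r as the product of the two, approximate coverage is 2Φ(1.96 r) − 1.

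| Filled per arm | m | r | Coverage of nominal 95% CI |
|---|---|---|---|
| 2 of 47 (4%) | 45 | sqrt(44/46) × sqrt(45/47) = 0.96 | 94% |
| 5 of 47 (11%) | 42 | sqrt(41/46) × sqrt(42/47) = 0.89 | 92% |
| 9 of 47 (19%) | 38 | sqrt(37/46) × sqrt(38/47) = 0.81 | 89% |
| 14 of 47 (30%) | 33 | sqrt(32/46) × sqrt(33/47) = 0.70 | 83% |

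In the last row, a 5% test of equal costs would reject about 17% of the time. A simulation of 20,000 trials with 30% of values filled at random in each arm gave 17.7%.

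**2. Choice of reference group**

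Let D be the observed difference between arm means and suppose the same share q is filled in each arm. With arm means, the estimate stays at D. With a pooled mean, each arm becomes (1−q) × its own mean + q × a common value, so the estimate becomes (1−q)D. At q = 0.30 that is 0.70 D.

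With a median fill, an arm's mean moves by q × (median − mean). For right-skewed costs the median lies below the mean, so the arm mean falls. The size depends on the skewness, which the article does not give.

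**3. Conditional case: a stopper's cost classed as missing**

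Assumptions: finishers cost the same in both arms, a stopper uses a fraction s of the course, a share d stops, and every stopper is filled with the finishers' mean. True mean cost as a share of a full course is (1−d) + d·s. The filled mean is 1.

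- With d = 0.30 and s = 0.5, the true mean is 0.70 + 0.15 = 0.85, and 1/0.85 = 1.18, so cost is overstated by 18%. At s = 0.7 the figure is 1/0.91 = 1.10. At s = 0.3 it is 1/0.79 = 1.27.
- With stopping of 20% in one arm and 40% in the other and s = 0.5, the true means are 0.90 and 0.80. After filling, both are 1 in expectation and the 10-point difference disappears. On a course of 10 to 20 sessions (10 weeks at one or two a week), that is 1.0 to 2.0 sessions per participant.
- A simulation with a finisher mean of 15 sessions and an assumed SD of 4 turned a true difference of 1.51 sessions into 0.01 under either an arm or a pooled mean.

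These figures apply only if stoppers' costs are in fact classed as missing.

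**The case against.** The strongest reply is that the rule fills only missing costs, and nothing in the article classes a stopper's cost as missing. Staff time is monitored at patient level and therapists record sessions in both arms, so someone who stops at week 4 has observed sessions up to then and none afterwards. **This stands.** A reader might infer that any difference in stopping between arms is necessarily erased from the cost comparison, and the documents do not support that.

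A reader might also infer from Table 1 that missing week 10 means a missing cost form. The N/A entry under participants, together with the use of hospital financial records and interviews with finance departments, means the form is not shown to be completed by patients.

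Nor is it right that nothing covers people who leave. Those who withdraw from the study are excluded, not filled with a finisher's cost. The conditional risk is therefore confined to people who stop treatment or miss week 10 without withdrawing.

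It can also be said that 30% is a recruitment allowance, and that the reference group may be specified in a fuller document. Both are fair, and the first is why the working shows a range. Neither rescues the rule itself. Single mean or median replacement, followed by ordinary intervals and tests, is a method the article states, and it understates uncertainty whenever any cost is filled.

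**Conclusion.** The concern holds for the replacement method. Intervals for the cost differences will be too narrow by an amount that grows with the share filled: slight at 2 of 47 per arm, about 92% coverage at 5 of 47, and about 83% at 14 of 47. These figures assume arm-mean fills and values missing at random. A pooled mean would also shrink an observed difference in proportion to the share filled, and a median fill would bias the mean of skewed costs. The actual share of missing costs is unknown.

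Loss of a stopping difference is only a possibility, limited to non-withdrawing stoppers whose costs are treated as missing. Its size and direction cannot be determined, because stopping by arm and unit costs are not given.

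This is a secondary objective of a feasibility study. It merits correction because the intervals are the stated basis for interpreting the cost comparison, and the correction is cheap.

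**What to change.** - **Cost what was delivered.** Cost each participant from the recorded sessions actually held and the hospital prices, with no session cost for sessions not held. State that early stopping is not missing cost.
- **Replace the fill rule.** For cost items incurred but unrecorded, use multiple imputation within arm in place of mean or median substitution, so that the uncertainty carries into the 95% CIs and tests. Report the number of imputed values by arm and cost category.
- **Reconcile the sections.** The cost rule, the exclusion of withdrawn participants' information and the intention-to-treat statement do not fit together. Say which participants enter the cost analysis and on what basis.

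The cost is a change of wording and modest extra analysis. Session data are already to be collected. The intervals will be wider.

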Low-cost and portable devices (average price: CAD $127.07 [US $104.16]) designed to offer specific hand therapies (eg, pronation or supination), such as *Rolyan Pronation/Supination* (CAD $188.57 [US $154.58]), or strengthen the forearm, such as *The Pronator* (CAD $108.64 [US $ 89.05]; a price list is available at Performance Health Trademarks [5]). The main disadvantage of these devices is that important measurements during hand therapy activities cannot be taken directly from them, and they are not adjustable.High-cost (portable and nonportable devices) commercial electromechanical devices designed to simulate the basic motions are required by the upper extremities in most occupations and to conduct hand therapy. This is the case for the Baltimore Therapeutic Equipment (BTE) work simulator and SaeboReJoyce [6]. For example, the estimated price of the BTE is between CAD $60,012.80 (US $49,193.99) and CAD $113,357.52 (US $92,921.99; email communication with the BTE Senior National Sales Representative) [7], whereas the SaeboReJoyce costs CAD $17,350.68 (US $14,222.79) [8]. The high cost of the BTE and SaeboReJoyce means that these devices are simply not affordable in many health care settings; thus, the FEPSim device could be a more affordable alternative for hand therapy purposes. The current prototype selling price of an FEPSim device is approximately CAD $6000 (US $4920; unit cost; eg, cost of goods sold). After evaluation and market analysis, to determine the scale of production, the FEPSim device should retail for less than CAD $1300 (US $ 1065.64) if the company adopts injection molding and brings in more purchased parts, with future models bringing costs down further. In addition, FEPSim has other potential advantages, such as compactness, portability, and ease of use.

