### Study Setting

The study will be conducted in 2 health care facilities: the Royal Alexandra Hospital Outpatient Clinic and the Glenrose Rehabilitation Hospital Specialized Rehabilitation Outpatient Program Hand Class. Both institutions are located in Edmonton, Alberta, Canada.

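### The plan sets a two-sample test and 95% CI for every cost category, but for equipment capital cost, depreciation and maintenance these cannot express the uncertainty that matters

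*Protocol article*

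**What the plan says.** The Data Analyses section for Secondary Objective 5 calls for descriptive statistics by cost category, then differences in means with 95% CIs, then a t test or Mann-Whitney U test at two-sided .05, "while looking for differences in each category of estimated costs between the comparator groups". Levels of uncertainty are to be interpreted from the intervals. No category is exempted and no other way of quantifying uncertainty is given.

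The Data Collection Methods section for the same objective lists seven categories:
- The first is staff time on sessions, which is monitored during the study.
- The second reads "the capital cost of the equipment used in each intervention and depreciation of the equipment will be calculated using the straight-line depreciation approach".
- The seventh is maintenance, including calibration and repair.

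On sources it says: "The information on the costs will be taken from the financial records at each hospital". Study Setting states: "The study will be conducted in 2 health care facilities". In Table 1 the participants entry for costs is N/A. Yet the same Data Collection section describes an "economic evaluation approach (patient-level data"), and the therapists record session length and frequency for both groups.

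Background and Rationale gives two device prices: "The current prototype selling price of an FEPSim device is approximately CAD $6000", and, if the manufacturing method changes, "the FEPSim device should retail for less than CAD $1300".

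**The concern.** A two-sample test and its CI measure sampling error between independent units. Session time varies from patient to patient and suits that method. Depreciation does not: it is a price divided by an assumed life, and maintenance is likewise a charge on equipment. Neither has between-patient sampling error of its own. The plan applies one method to both kinds of category and reads uncertainty from the result.

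The Discussion says the cost estimates are meant for people who make purchasing decisions and manage hospital budgets. Equipment is the category in which the arms differ by design. An interval that leaves out price, useful life and throughput could be taken by such readers as the full uncertainty about what the device costs per patient.

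**Working it through.** The protocol gives no number of observations, SD or precision for the cost analysis, so there is no stated figure to reproduce. The check asks what the prescribed CI would contain under each way of assigning a hospital-level cost.

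**Inputs from the protocol.** Two hospitals; a recruitment target of 47 per arm with 30% dropout (47 × 0.7 ≈ 33 remaining); 9 months of data collection (0.75 year); prices of about CAD 6000 and below CAD 1300.

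**Assumed, because the protocol is silent.** One FEPSim device per hospital; useful life of 3, 5 or 10 years; the example costs in routes 1 and 2; the variation in use in route 3.

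**Route 1: one hospital figure copied to each patient.** Suppose standard equipment costs CAD 100 per patient at one hospital and CAD 110 at the other, and the device adds CAD 10 at both. With 24 and 23 patients per arm:
- Within-arm variance = 10² × (24 × 23/47)/46 = 25.5.
- SE of the difference = √(2 × 25.5/47) = 1.04.
- 95% CI = 10 ± 1.986 × 1.04 = 7.9 to 12.1, P about 2e-15.

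The interval is narrow only because four numbers have been repeated.

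**Route 2: the same figures kept at hospital level.** There are two values per arm and 2 degrees of freedom.
- SD within arm = 7.07; SE = √(50/2 + 50/2) = 7.07.
- 95% CI = 10 ± 4.303 × 7.07 = −20.4 to 40.4, P = 0.29.

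At equal SD, the half-width relative to 47 values per arm is 4.303/(1.986 × √(2/47)) = 10.5. With 33 per arm it is 8.7. In this example the difference is exactly CAD 10 in each hospital, so the change from ±2.1 to ±30.4 comes from how the figures are counted and not from any evidence.

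**Route 3: a fixed unit cost multiplied by each patient's recorded use.** A simulation with 47 per arm, 10 to 20 sessions per patient, the same unit cost in both arms and 5,000 runs gave a type I error of 4.9%. The test is valid for fixed unit costs. What the interval measures is session use. For one arm's mean cost the relative half-width is t × CV/√n. With an assumed CV of 33% and n = 47 this is 2.01 × 0.33/√47 = 9.7%. Price, life and patients per device do not enter. Changing the assumed life from 5 to 3 years alone raises the cost by 5/3 − 1 = 67%, and changing it to 10 years halves it.

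**Size of what is left out.** FEPSim depreciation per intervention patient = 2 devices × (price/life) × 0.75/47:

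| Price scenario | 3 years | 5 years | 10 years |
|---|---|---|---|
| CAD 6000 (current prototype) | 63.8 | 38.3 | 19.1 |
| CAD 1300 (ceiling of conditional future retail price) | 13.8 | 8.3 | 4.1 |

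Within either scenario, useful life alone moves the figure by a factor of 10/3 = 3.3. Fewer patients per device raise it in proportion: 33 instead of 47 multiplies every entry by 47/33 = 1.42.

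**The case against.** The strongest defence is route 3. The protocol calls its approach patient-level and has session length and frequency recorded, so multiplying a unit cost by each patient's own use is a natural reading. Costing measured use at a fixed price is ordinary practice, and test size is then correct. The assignment rule is also a detail that a condensed article may leave to a fuller document. All of this stands, so no error can be charged for the missing rule or for hospital unit prices as such.

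A reader might infer that the plan will treat each hospital figure as 94 independent patient values and so produce grossly inflated false-positive rates or vanishingly small P values. The documents do not support that. They state no unit of analysis for the cost tests, and 94 is the recruitment target before dropout. Simulations that inflate type I error this way let the four hospital-by-arm cells vary independently. That is a worst case, because both arms run in both hospitals and shared hospital costs can largely cancel in the arm difference.

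The two prices also cannot be read as a sampling range. One is current and the other is a conditional future price, so they are separate scenarios.

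Finally, the sums are small. Ten weeks of one or two sessions of 30 to 45 minutes is 5 to 15 therapist hours. At an assumed CAD 30 to 50 per hour (the protocol gives no salaries) that is about CAD 150 to 750 per patient, generally well above the equipment figures, and the analysis of session time is unaffected.

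What remains is the instruction itself: a test and CI for each category, as the only stated measure of uncertainty.

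**Conclusion.** The point holds in limited form. For capital cost, depreciation and maintenance, the prescribed CI and P value are falsely narrow, nearly empty, or confined to session-time variation, depending on an assignment rule that the article does not state. In no case do they carry uncertainty in price, useful life or patients per device. It should not be read as a finding that the trial will report pseudo-replicated significance, since that depends on copying hospital figures to patients, which is nowhere stated.

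The illustrated spread of about CAD 4 to 64 per patient rests on one device per hospital, 9 months of use, 47 intervention patients, lives of 3 to 10 years and the two price scenarios. It is no estimate of this trial's cost difference. The change is cheap and worth making, but its weight is modest: costs are the fifth secondary objective of a feasibility study, and descriptive summaries by category are already planned.

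**What to change.** In the Data Analyses section for Secondary Objective 5:
- Keep the t or Mann-Whitney tests and the 95% CIs for resources measured on each patient (staff time on sessions, supplies and consumables) and, if reported, for total cost per patient.
- Report capital cost, depreciation and maintenance descriptively as a cost per patient, without a test or CI.
- Add a deterministic sensitivity analysis of those categories over useful life, patients per device and the two price scenarios in Background and Rationale (about CAD 6000 for the current prototype, below CAD 1300 for the conditional future retail price), labelled as scenarios.

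This takes one or two sentences and a small table, and needs no new data. What is lost is a formal P value for the equipment and maintenance categories.
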